### Process evaluation

A number of strategies are planned to monitor intervention uptake, assess adherence to protocols and describe experiences with trial implementation.

#### Measures of intervention exposure

SILC-MCHN home visits: number of women identified as eligible; number of women who decline a visit; number of visits; timing of visits; and time spent during visits.

Drop-in centres: number of women who visit drop-in centres, reason for the visit and total number of visits to each drop-in centre.

#### Adherence to protocols

SILC-MCHNs will keep a log of what is provided to women during visits. Breastfeeding concerns women raise or issues identified by the providers will be documented on pre-coded data sheets at home visits and drop-in centres.

SILC-MCHNs will attend a total of four workshops during the trial period: one before implementation of the interventions and three while the interventions are in place to discuss adherence to SILC protocols, review processes and discuss any concerns SILC-MCHNs may have. Research team members will visit LGAs at regular intervals (estimated to be 3–5 times) during the intervention period, to monitor protocol adherence and discuss concerns about intervention implementation with SILC-MCHNs and MCH co-ordinators.

#### Intervention implementation evaluation by SILC-MCHNs and MCH co-ordinators

An evaluation of how the interventions have been carried out will be undertaken using surveys and focus groups with SILC-MCHNs and MCH co-ordinators. SILC-MCHNs attending the final SILC workshop at the conclusion of the intervention will be invited to participate in focus groups and complete a structured questionnaire including open-ended questions. The questionnaire will explore their views and experiences of being a SILC-MCHN. They will be able to report on any highlights, any problems or barriers in implementation of the interventions, and to make recommendations on the improvement of intervention implementation. There will be two focus groups led by the research team – one group for SILC-MCHNs from Trial arm 1 and the other group for SILC-MCHNs from Trial arm 2. Focus groups will give SILC-MCHNs an opportunity to reflect on and discuss their experiences of participating in the SILC interventions.

Face-to-face interviews will be conducted with MCH co-ordinators and managers from intervention LGAs. These interviews will provide an opportunity for participants to share their experiences and to provide information regarding problems or barriers to the introduction and embedding of the interventions, which will be important in terms of sustainability if the interventions are shown to be effective.

### Sample size

Infant feeding outcomes are routinely collected by the MCHNs at KAS visits, and include infant feeding at hospital discharge, two weeks, three months (asked at the four months KAS visit) and six months postpartum (asked at eight months KAS visit). Given the non-contemporaneous nature of ascertainment of the infant feeding outcomes and that breastfeeding at four months is a key national indicator of children’s health, the four month KAS visit was determined the most appropriate time to collect infant feeding outcome data. The standard MCH questions related to infant feeding have the potential for misclassification of infant feeding outcomes, therefore a new question on infant feeding will be added to the data collected at the four month KAS visit that provides a cross-sectional snapshot of the percentage of infants receiving *any* breast milk (‘in the last 24 hours’). Our primary outcome measure is thus the percentage of infants receiving *any* breast milk at four months.

There are no local representative data on infant feeding outcomes at four months, so we estimated the four month figures from three and six-month state-wide infant feeding data. We plan to include only LGAs with breastfeeding rates below the state average at hospital discharge and with more than 450 births per annum, so we used the most recent data available (2008/2009) to identify potentially eligible LGAs and calculate their breastfeeding rates [34]. The state average for *any* breastfeeding at hospital discharge was 87%, and for the LGAs whose rate was less than the state average, the average rate of *any* breastfeeding at hospital discharge was 81%. We then used the rate of *any* breastfeeding at three months in this group of LGAs (53%) and any breastfeeding at six months (39%) to estimate a figure for four months. We consider the drop is likely to be continuous, so estimate that 48% are giving *any* breast milk at four months.

While the unit of randomisation is the LGA, the MCH centres form the clusters. We aim to have the power to detect an increase in the overall breastfeeding rates at four months from 48% to 58%. With this change and assuming a standard error for the average breastfeeding rate in each LGA of 5%, sample size estimates show that we need approximately 4 LGAs in each trial arm. To achieve this standard error we need to have 374 women in each arm (without allowing for clustering). Given that we will be obtaining breastfeeding data on all women in each LGA, with an estimated average of about 1000 births per LGA per annum, we can obtain the required sample size allowing for an inflation factor of approximately 2.7 (1000/374), which if the *geometric* mean number of MCH centres is 86 (calculated on data from MCH centres in the potentially eligible LGAs), allows for an intra-cluster correlation (ICC, ρ) of 0.02 (2.70= 1 + 85*ρ). We could not identify relevant literature on which to base our estimate for the ICC in breastfeeding trials, therefore we used the conservative estimate of 0.02 which is larger than ICCs found in cluster trials for smoking cessation in pregnancy [42]. This was also consistent with the variation we found in state-wide MCH data.

Calculating the number of women who will be eligible to potentially receive the intervention is based on the fact that the proposed intervention will only have the ability to affect women who are breastfeeding at discharge, so to gain this 10% increase overall (i.e. 48% to 58%) we will need to increase the rate of breastfeeding from 59% (or 48%/81%*100) to 72% (58%/81%*100) among those who are breastfeeding at hospital discharge. For a simple random sample this would require 224 women per each intervention trial arm (with alpha 0.05 and 80% power), i.e. 448 in total. Taking into consideration the potential effect of clustering we have inflated the sample size assuming an intra-cluster correlation (rho) of 0.02 (as discussed above), so we require approximately 400–500 women in each intervention arm.

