#### Outcome variables

The primary outcome of the study is *any* breastfeeding at four months. A single data item asking about *infant feeding* ‘in the last 24 hours’ will be used to ascertain this outcome at the routine four month KAS visit. The four month KAS participation rate from the last state-wide report was 93.6% [43]. Three and six month infant feeding outcomes will be obtained from routinely collected MCH centre infant feeding data collected at the four month and eight month KAS visits respectively. The eight month KAS participation rate from the last state-wide report was 85.6% [43].

Other variables of interest (or potential confounders for the primary outcome) which will be abstracted from routinely collected MCH data are:Gestational age of infant at birth;Date of birth of infant;Parity of mother;Mode of birth (vaginal, caesarean delivery);Age of mother;Date of the routine four month KAS visitInfant age in weeks at the routine four month KAS visit;Health Care Card [proxy for socioeconomic status];Aboriginal/Torres Strait Islander status of mother;Country of birth of mother;Year mother arrived from overseas (where relevant);Country of birth of father; andMCH centre postcode.

For the secondary aims of the study, addressed via the survey exploring women’s satisfaction with the breastfeeding support they received, the following variables will be collected:Infant feeding at six months;Introduction of solids;Infant feeding intention;Breastfeeding complications, such as milk supply issues, nipple pain and mastitis;Reasons for not commencing breastfeeding;Reasons for ceasing breastfeeding;Breastfeeding support after discharge (domiciliary visits, Lactation Consultant, MCHN, SILC-MCHN, MCH line, ABA, breastfeeding drop-in centre);Woman’s knowledge of community breastfeeding services available (SILC-MCHN, breastfeeding drop-in centre); andBackground data such as maternal age, marital status, education, income level, employment status, smoking status, and maternal height and weight.

Intervention implementation – process and impact measures:Assessment of adherence to intervention protocols;Evaluation of the SILC trial via surveys and focus groups with SILC-MCHNs; andInterviews with MCH co-ordinators.

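### The clustering allowance counts every birth as an outcome, although the primary outcome exists only for infants seen at the four-month visit (93.6% state-wide); the covered ICC is about 0.018 to 0.019, slightly below the stated 0.02

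*Protocol article*

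**What the plan says.** All references are to the protocol article.

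- **Sample size, target.** The aim is to "detect an increase in the overall breastfeeding rates at four months from 48% to 58" per cent.
- **Sample size, unclustered number.** The text ties this to LGA-level precision: "assuming a standard error for the average breastfeeding rate in each LGA of 5%, sample size estimates show that we need approximately 4 LGAs" per arm. It continues: "To achieve this standard error we need to have 374 women in each arm (without allowing for clustering").
- **Sample size, births available.** The supply side rests on the premise "Given that we will be obtaining breastfeeding data on all women in each LGA". For the size of an LGA the section works "with an estimated average of about 1000 births per LGA per annum". From this it concludes that the requirement can be met, "allowing for an inflation factor of approximately 2.7 (1000/374"). With 86 in the place of the cluster size, it solves 2.70 = 1 + 85ρ and reports an ICC of 0.02.
- **Sample size, second calculation.** Among women breastfeeding at discharge (59% to 72%), 224 per arm are needed at 80% power, raised to 400 to 500 for clustering.
- **Outcome variables.** The single feeding item "will be used to ascertain this outcome at the routine four month KAS visit". The same paragraph says "The four month KAS participation rate from the last state-wide report was 93.6" per cent.

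The Sample size section also names the four-month KAS visit as the point of collection, but neither calculation makes an allowance for infants who do not attend.

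**The concern.** An infant not brought to the four-month visit has no primary outcome. The premise of complete data and the 93.6% participation figure therefore cannot both hold, and the premise enters a printed calculation: the numerator of 1000/374 is births, while the denominator is women whose outcome is known.

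What is at stake is the statement that the births available cover an ICC of 0.02. The section says that no relevant literature on ICCs in breastfeeding trials was found, and it presents 0.02 as conservative. The room around that value therefore matters to a reader judging the design. The calculation also has no slack, because the inflation factor was found by dividing what is available by what is needed. Any loss of outcomes lowers the covered ICC directly.

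**Working it through.** **Inputs.** From Sample size: 1000 births per LGA per year, 374 women required before clustering, cluster size 86 (read as the cluster size because the formula uses 85 = 86 − 1), ICC 0.02. From Outcome variables: participation 0.936. The 374 is taken as stated; standard two-proportion formulas for 48% v 58% at two-sided 5% and 80% power give 387 to 410, and nothing below depends on which is right.

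**Formula.** Inflation factor F = outcomes available / 374. Covered ICC = (F − 1)/(m − 1), where m is the cluster size.

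**Step 1: reproduce the plan.**
F = 1000/374 = 2.674 (printed as about 2.7).
ICC = 1.674/85 = 0.0197 (printed as 0.02).

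**Step 2: count outcomes instead of births.**
1000 × 0.936 = 936.
F = 936/374 = 2.503.
- Cluster size kept at 86: ICC = 1.503/85 = 0.0177.
- Cluster size reduced in the same proportion, 86 × 0.936 = 80.5: ICC = 1.503/79.5 = 0.0189.

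The article does not say whether 86 counts births or attending infants, so both are shown.

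**Step 3: the same check from the demand side, at ICC 0.02.**
- m = 86: outcomes needed = 374 × 2.70 = 1010. The 1000 births are already 1% short, and 936 outcomes are about 7% short.
- m = 80.5: factor 1 + 79.5 × 0.02 = 2.59; outcomes needed = 374 × 2.59 = 969. The 936 outcomes are about 3% short.

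**Step 4: range for attendance.** The rate in the trial LGAs is not given. The rows other than 93.6% are illustrative assumptions, with m = 86.

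| Attendance | F | Covered ICC |
|---|---|---|
| 95% | 950/374 = 2.540 | 0.0181 |
| 93.6% | 2.503 | 0.0177 |
| 90% | 900/374 = 2.406 | 0.0165 |
| 85% | 850/374 = 2.273 | 0.0150 |

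**Step 5: what does not change.** The sample-size formulas give numbers of women with a known outcome. The continuity-corrected formula for 59% v 72% at two-sided 5% and 80% power returns exactly 224. Non-attendance alters only the births that must occur to yield such numbers: 374/0.936 = 399.6, about 400; 224/0.936 = 239.3, about 240; 400 to 500 becomes about 427 to 534.

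**The case against.** The strongest reply is that this is a slip of wording with little effect.

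- **Reading of the premise.** Data on all women may mean routine data on everyone rather than on a drawn sample, and the article openly names the visit and its participation rate. Nothing is concealed, but the division still uses 1000 as if ascertainment were complete.
- **Rounding.** The figures are given as approximate, and both 0.0177 and 0.0189 round to 0.02. That is true, and it is why the effect is called modest. The factor printed as 2.70 in the equation, however, does not survive as 2.50.
- **Spare capacity.** The ratio sets births in one LGA against women per arm, while about 4 LGAs per arm are planned. Four LGAs would give 4 × 936 = 3744 outcomes against about 1010 needed. If clustering within Maternal and Child Health centres is all that matters, power for 48% v 58% exceeds 0.99 with or without the loss. This stands as a reason not to claim that the trial is too small. It is less reassuring on the section's own assumption of a 5% standard error per LGA, where 4 LGAs per arm give power of about 0.81. It also does not repair the printed ratio.

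A reader might go further and infer that the required numbers are too low, or that the 80% power is overstated. The article does not support either. The numbers 374, 224 and 400 to 500 are outcomes needed. The 80% is attached only to 224, not to 374. A lower power appears only if those numbers are reread as births, which the text does not say. Even then, 224 × 0.936 is about 210 outcomes, which still give power of 0.80 for 59% v 72% without continuity correction.

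**Conclusion.** The point holds as a small inconsistency in a stated premise and in the factor derived from it. The clustering allowance treats about 1000 births as 1000 outcomes, whereas the article's own participation figure gives about 936. The inflation factor is then about 2.50 rather than 2.7. The covered ICC is 0.0177 (m = 86) to 0.0189 (m about 80.5), against 0.0197 on the plan's arithmetic and 0.02 as printed.

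This assumes that state-wide attendance applies in the trial LGAs and takes 374, 1000 births and 86 as stated. No required number is wrong on this account, no stated power is shown to be false, and no design or analysis decision turns on it.

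The point is separate from how many months of births can be counted. If that count is revised, the 0.936 applies on top. For example, seven usable months (nine months less the two-month run-in) would give 1000 × 7/12 = 583 births, and 583 × 0.936 = 546 outcomes.

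**What to change.** In Sample size, replace the premise of data on all women by data on infants attending the four-month KAS visit (93.6% state-wide), and say that this rate is assumed for the trial LGAs. Apply 0.936 once, to the births available: 936/374, a factor of about 2.5, and a covered ICC of about 0.018 to 0.019, stating which cluster size is used. If the calculation is revised for other reasons, carry 0.936 through the revised version.

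Leave 374 and 224 as outcomes needed. If births needed are also quoted, give them separately (about 400 and 240 before clustering). Do not both raise 374 to 400 and lower 1000 to 936: 936/400 = 2.34 would count the same loss twice.

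The cost is one sentence and slightly less favourable printed figures. Trial status reports that data collection is complete, so no additional participants are involved.

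### The 224 women per arm come from rates rounded outward (59.26% to 59%, 71.60% to 72%), so they are sized for a 10.5-point overall gain, not the stated 10; the same formula on the unrounded rates gives 248

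*Protocol article*

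**What the plan says.** The Sample size section of the protocol article sizes the trial in two steps.

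The first step concerns all infants in an LGA. The target is stated as: "We aim to have the power to detect an increase in the overall breastfeeding rates at four months from 48% to 58" per cent. It leads to about four LGAs per arm, from a base of 374 women and an inflation factor of about 2.7.

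The second step concerns only women who leave hospital breastfeeding, because only they can be affected by the intervention. The section gives their share in the LGAs below the state average: "the average rate of *any* breastfeeding at hospital discharge was 81" per cent. To deliver the same overall change, it says that breastfeeding must rise "from 59% (or 48%/81%*100) to 72% (58%/81%*100) among those who are breastfeeding at hospital discharge". For these rates it gives a simple-random-sample size: "this would require 224 women per each intervention trial arm (with alpha 0.05 and 80% power), i.e. 448 in total". It then inflates for clustering with an intra-cluster correlation of 0.02 and concludes: "so we require approximately 400–500 women in each intervention arm".

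**The concern.** The protocol prints the fractions 48/81 and 58/81 beside the rounded results. The lower quotient is rounded down and the higher one up, so both roundings widen the effect to be detected. Each is an ordinary rounding to the nearest whole percentage. Required sample size, however, varies roughly with the inverse square of the difference, so two small shifts in opposite directions are enough to move it visibly.

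If the rounded rates went into the formula, 224 belongs to a larger effect than the 48% to 58% change that the same sentence says it delivers. The claim of "with alpha 0.05 and 80% power" would then not hold for the stated target. The shortfall would also pass into the clustering-inflated number, which is built on 224.

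**Working it through.** **Inputs, all from the Sample size section**
- Overall rates at four months: 48% and 58%.
- Any breastfeeding at discharge: 81%.
- Rates as printed: 59% and 72%.
- Alpha 0.05 and power 80%. Sidedness is not stated; two-sided is assumed because it reproduces the figure.
- Equal arms: 2 × 224 = 448.

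**Step 1. The conversion**
- 48/81 = 59.26% and 58/81 = 71.60%. The difference is 10/81 = 12.35 points.
- As printed: 72 − 59 = 13 points.
- Mapped back to all infants: 0.59 × 0.81 = 47.79% and 0.72 × 0.81 = 58.32%. The gain is 0.13 × 0.81 = 10.53 points, not 10.

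**Step 2. The formula**

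With d = p2 − p1 and p̄ the mean of p1 and p2:

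n = [1.960 √(2p̄(1−p̄)) + 0.842 √(p1(1−p1) + p2(1−p2))]² / d²

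With continuity correction: n_c = (n/4) × [1 + √(1 + 4/(n d))]²

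**Step 3. Reproducing the protocol's figure (59% v 72%)**
- n = (1.3176 + 0.5605)² / 0.13² = 208.7, so 209.
- n_c = 223.8, so **224**, as stated.
- Other versions on the same rates do not give 224: 206 unpooled, 209 by the arcsine method, and 165 or 180 one-sided (uncorrected or corrected).

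**Step 4. The same formula on the unrounded rates (48/81 v 58/81)**
- n = (1.3182 + 0.5613)² / 0.12346² = 231.8, so 232.
- n_c = 247.7, so **248**.

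| Rates | Uncorrected | Continuity-corrected |
|---|---|---|
| 59% v 72% | 209 | 224 |
| 48/81 v 58/81 | 232 | 248 |
| Increase | 11% | 11% |

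The like-for-like gap is 248 − 224 = 24 women per arm. This is 24/224 = 10.7% more than stated; equivalently, 224 is 24/248 = 9.7% below the need.

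**Step 5. Power of 224 per arm, before clustering**

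Power = Φ{[(d − c)√n − 1.960 √(2p̄(1−p̄))] / √(p1(1−p1) + p2(1−p2))}, with c = 1/n for the continuity-corrected version and c = 0 otherwise.
- 59% v 72%: 80.0% corrected (82.7% uncorrected).
- 48/81 v 58/81: **75.6%** corrected (**78.6%** uncorrected).

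**Step 6. Effect on the inflated range**
- The stated 400 to 500 implies factors of 400/224 = 1.79 and 500/224 = 2.23.
- Applied to 248, the unrounded factors give about 443 to 554.

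**The case against.** **The figure is right for the rates printed beside it.** Both rates are correctly rounded, their derivation is shown, and 224 follows from them. This stands as a description of how 224 arose. It does not rescue the sentence, which says that these rates correspond to the 48% to 58% change; they correspond to 47.8% and 58.3%.

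**The power loss depends on the formula.** The protocol does not mention a continuity correction, and the planned analysis is logistic regression. Without the correction the unrounded requirement is 232, only 8 women or 3.6% above 224, and the power is 78.6%. This stands: the conservative correction absorbs most of the rounding. The 11% applies only when the method that produced 224 is kept.

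**The inputs are approximate.** The 48% is interpolated from three- and six-month rates, and the 81% is itself a rounded average. Letting the 81% vary from 80.5% to 81.5% moves the corrected size only from about 243 to 252, so this does not lead back to 224.

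**The end result is a loose range.** 443 to 554 largely overlaps 400 to 500. This stands too and limits the practical weight of the point.

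Two stronger readings may tempt a reader.
- That the total of 448 leaves out the comparison arm. The text does not support this as an error: 448 reads naturally as one pairwise comparison, which is how the Data analysis section compares the arms, or as the two intervention arms together.
- That the true requirement is 670 per arm against 400 to 500. Applying the 2.7 factor to 248 does give 670, but 224 × 2.7 is already 605. Most of that gap comes from the choice of inflation factor, a separate matter; rounding accounts for about 65 women.

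**Conclusion.** The stated 224 per arm and 80% power do not follow from the stated 10-point target. On the method that reproduces 224, the target needs 248 per arm, and 224 gives 75.6% power. Without the continuity correction the corresponding figures are 232 and 78.6%, so the stated power is missed on either basis, by 4.4 or 1.4 points. This assumes a two-sided 0.05 test, equal arms and no clustering.

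The point is minor. A reader might infer that the trial is underpowered, but the documents do not support that from this error alone. Breastfeeding data are to be obtained on all women in each LGA, at about 1000 births per LGA a year, and the LGA-level sizing earlier in the section does not use the 59% and 72%. What is wrong is a printed sample size and its power claim, not the scale of the trial.

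**What to change.** Either of two changes to the Sample size section would settle it.
- Recompute from the unrounded rates and give 248 women per arm before clustering (2 × 248 = 496 for one pairwise comparison). Carry this into the inflated figure, about 443 to 554 at the factors implied by the present range. State that the test is two-sided and continuity-corrected.
- Or keep 224 and state that it has 80% power (two-sided, continuity-corrected) for a rise from 59% to 72% among women breastfeeding at discharge, which is a 10.5-point gain overall.

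The cost is one or two sentences. No extra recruitment or change of design follows, because outcomes are collected on all women in the participating LGAs. The first option makes the stated requirement slightly less favourable. As the article reports data collection as complete, the correction would go into the reporting of the sample-size rationale.

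### The stated need for 400–500 women per intervention arm does not follow from 224 women and the only design effect in the plan, which give about 605

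*Protocol article*

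**What the plan says.** All of this is in the protocol article, section Sample size.

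- **All women, 48% to 58%.** With about 1000 births per LGA per year, the article says "we can obtain the required sample size allowing for an inflation factor of approximately 2.7 (1000/374"). It matches this factor to a cluster term of 86 and an intra-cluster correlation of 0.02, so that 1 + 85 × 0.02 = 2.70.
- **Women breastfeeding at discharge.** Dividing by the 81% who leave hospital breastfeeding, the plan needs to "increase the rate of breastfeeding from 59% (or 48%/81%*100) to 72% (58%/81%*100"). It continues: "For a simple random sample this would require 224 women per each intervention trial arm", at alpha 0.05 and 80% power, "i.e. 448 in total".
- **Inflation of the second calculation.** The authors say they have "inflated the sample size assuming an intra-cluster correlation (rho) of 0.02 (as discussed above"), "so we require approximately 400–500 women in each intervention arm".

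No second cluster size or design effect is given for the last step.

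**The concern.** The last step starts from a stated number (224) and a stated correlation (0.02), and it refers back to a discussion that contains one cluster term and one design effect. The product of 224 and that design effect lies well above the stated range.

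This is the only clustered requirement given for the women whom the article says the interventions can affect. A reader who uses it to judge whether an arm is large enough would accept a number that falls short of 80% power on the plan's own assumptions.

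**Working it through.** **Inputs** (protocol article): rates 59% and 72%, alpha 0.05, power 80%, 224 per arm, correlation 0.02, cluster term 86, and 81% breastfeeding at discharge (Sample size); intervention of 9 to 12 months with the first two months excluded from analysis (Data collection). The article does not say whether alpha is one- or two-sided. Two-sided is assumed because it reproduces 224.

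**Step 1: reproduce 224.** With p1 = 0.59, p2 = 0.72, d = 0.13 and mean p = 0.655:

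n = [1.96 √(2 × 0.655 × 0.345) + 0.84 √(0.59 × 0.41 + 0.72 × 0.28)]² / 0.13² = 208.7

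With continuity correction: (208.7/4) × [1 + √(1 + 4/(208.7 × 0.13))]² = 223.8, i.e. 224. This matches the plan.

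**Step 2: inflate.** n × [1 + (m − 1) × ICC] with m = 86 and ICC = 0.02 gives 224 × 2.70 = 604.8, i.e. 605. That is 21% above 500 and 51% above 400. Starting from the uncorrected 209 gives 564, also outside the range.

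**Step 3: what the range implies.**

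- Design effect: 400/224 = 1.79 and 500/224 = 2.23.
- Cluster size at ICC 0.02: 1 + 0.786/0.02 = 40.3 and 1 + 1.232/0.02 = 62.6.
- Or, keeping m = 86, an ICC of 0.786/85 = 0.009 to 1.232/85 = 0.014.

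None of these values is in the article.

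**Step 4: smaller clusters that could be built from the article's figures.**

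| Cluster size | Design effect | 224 × design effect |
|---|---|---|
| 86 | 2.70 | 605 |
| 86 × 0.81 = 69.7 | 2.37 | 532 |
| 86 × 0.81 × 10/12 = 58.1 | 2.14 | 480 |
| 86 × 0.81 × 9/12 = 52.2 | 2.02 | 454 |
| 86 × 0.81 × 7/12 = 40.6 | 1.79 | 402 |

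The 81% restriction alone stays above 500. The range is reached only when a shortened period is applied as well, and only if 86 is an annual figure, which is an assumption.

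**Step 5: power at design effect 2.70, 59% against 72%.**

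| Women per arm | Effective women | Power, with correction | Power, without |
|---|---|---|---|
| 400 | 148 | 61% | 65% |
| 500 | 185 | 71% | 75% |
| 605 | 224 | 80% | 83% |

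**Step 6: rounding, as a sensitivity check.** 48/81 = 59.3% and 58/81 = 71.6%, a gap of 12.3 points rather than 13. The same corrected formula then gives 248 per arm instead of 224.

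**The case against.** The best defence is that the sentence carries forward the correlation and not the factor 2.70. That factor was built for all births over a year, whereas this step concerns only women breastfeeding at discharge, accrued over a shorter period. A smaller cluster is therefore a reasonable input. With 81% and 7–10 analysable months the result is 402–480, which fits the range and would explain why a range is given at all.

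This stands in part. It means that 605 need not be the only defensible figure. It does not make the printed chain sound, because the sample size section mentions neither scaling at this step, and the cluster discussion it refers back to uses 86 and annual births. Nor can one calculation be shortened and the other left alone. On a full year the earlier comparison balances: 1000/374 = 2.67 against 2.70. On seven months, in the same form, it would be 583/374 = 1.56 against 1 + (50.2 − 1) × 0.02 = 1.98.

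Two stronger readings are tempting, and the article does not support them.

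- **That the trial is short of women.** Outcome data are planned for all women in each LGA. With three LGAs per intervention arm (section Trial status) and, as an assumption, average-sized LGAs over seven months, 3 × 1000 × 7/12 × 0.81 is about 1,418 women breastfeeding at discharge. At the quoted 93.6% attendance at the four-month visit, about 1,327 remain.
- **That the right figure is 248 × 2.70, about 670.** The 59% and 72% are openly stated rounded planning values, and the 48% behind them is an interpolation between 53% and 39%. Half a point of rounding is small beside that uncertainty.

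**Conclusion.** The point holds as an error in the stated justification. From 224 women and the plan's only design effect, the requirement is about 605 per intervention arm, not 400–500. If 400–500 women were all that was analysed at that design effect, power would be about 61–71% (65–75% without continuity correction) against the stated 80%.

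This rests on a two-sided 5% test, the rounded rates, an ICC of 0.02 and a cluster size of 86. If a smaller cluster was intended, the range may be right, but its essential input is missing and its basis differs from that of the preceding calculation. The power figures describe the printed requirement; they do not forecast the trial's power.

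**What to change.** Do one of the following in the sample size section:

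1. State the requirement as about 605 women per intervention arm, shown as 224 × 2.70.
2. If a smaller cluster size was used, print it with its derivation (share breastfeeding at discharge, months of accrual) and the resulting design effect, and put the earlier 1000/374 comparison on the same accrual period.

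Optionally, add that unrounded rates give 248 rather than 224 before clustering. The cost is one corrected figure or one or two added sentences. No extra enrolment is needed, since data are planned for all births in the participating LGAs.
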